### Interim analyses {21b}

Interim analyses are not planned in this low-risk intervention consisting of providing information through a device.

### Methods for additional analyses (e.g. subgroup analyses) {20b}

No other additional or subgroup analyses are planned in this study.

### Methods in analysis to handle protocol non-adherence and any statistical methods to handle missing data {20c}

The main analysis is performed as “intention to treat.” All randomised subjects with an available main outcome will be analysed in the group to which they were randomised, regardless of whether they received the assigned intervention. Reasons for dropping out of the study are recorded in a data file and described in detail. A multiple imputation technique will be used for missing data.

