### Outcomes {12}

The primary outcome of the study is the difference between the intervention and control groups in terms of caregivers’ self-reported state anxiety. It is be measured using the State-Trait Anxiety Inventory form Y questionnaire [21] in the surgical department, before the caregiver and child go into the operating theatre on the day of surgery, approximately seven days after enrolment.

Secondary outcomes are:The difference between the intervention and control groups in caregiver preparation for hospitalisation and surgery, evaluated at arrival at the hospital using a checklist completed by the administrative nurse (e.g. number of documents missing on arrival) approximately 5 days after enrolment;The difference between the intervention and control groups in preparing children for surgery, evaluated by ORL surgical nurses on arrival at the surgical department, approximately 5 days after enrolment;The difference between the intervention and control groups in terms of children’s distress. It is assessed by ORL surgical nurses in the surgical department using the modified Yale Preoperative Anxiety Scale [22];The difference between the intervention and control groups in self-reported primary caregiver anxiety as measured by the State-Trait Anxiety Inventory form Y questionnaire [21] on the day of follow-up, around the seventh day after surgery and 13 days after enrolment.The difference between the intervention and control groups in terms of the social and health effects of the introduction of an mHealth app in a maternal and child hospital. It is evaluated on the day of follow-up, approximately 14 days after enrolment.

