### Sample size {14}

Assuming a mean score of preoperative anxiety (main outcome of the study) of 50 for the control group, with a standard deviation (SD) of 13 [21], and a mean of 45 for the intervention group, with SD of 10 (effect size = 0.43), an alpha value of 0.05 and a beta value of 0.20, 180 subjects (90 per group) are needed to conduct the study (G*power, Wilcoxon-Mann–Whitney test, two groups).

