
Caregivers are asked to complete both forms at T0 to determine anxiety trait and baseline levels. The state form of the STAI Form Y-1 is completed in the hospital surgical department prior to surgery at T2 and again on the seventh day after surgery (follow-up) at T3 to measure study outcomes**.**The modified Yale Preoperative Anxiety Scale (mYPAS) [22] is used as an observational tool to measure anxiety in children in the preoperative period at T2. The mYPAS consists of 27 items that examine five domains, such as child activity, emotional expressiveness, arousal state, vocalisation, and caregiver engagement. Scores range from 23.33 to 100, with higher scores indicating higher levels of anxiety. The tool is completed by nurses. Since there is no validated Italian version of the questionnaire, only English-speaking nurses are responsible for completing the instrument, according to Liguori and colleagues [24].The social and health impact of the study is self-assessed by caregivers at follow-up (T3) through outcome measures, such as how often caregivers had to call the hospital for additional information, had to visit the paediatric Emergency department, or had other complications at home after surgery (e.g. bleeding, uncontrolled pain).

The questionnaires at T0 and T2 are completed online via a tablet available to participants in groups A and B and to nurses in the surgical department. The assessment at T1 is completed in paper form. Moreover, considering that in this hospital not all caregivers bring their child for follow-up, sometimes preferring to see their general paediatrician, data collection at T3 is performed online after sending caregivers an email with a link to fill out the questionnaires.

Prior to the start of the study, nurses in the surgical department participating in the study were trained in the use of the assessment tools (e.g. mYPAS) with standardised instructions. The training was conducted by a nurse from the research ream in a meeting room of the department.

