## Statistical methods

### Statistical methods for primary and secondary outcomes {20a}

Description of the categorical variables will be made using frequency and percentage while mean and standard deviation (or median and interquartile range if variables are not normal) will be reported for continuous variables. Data will be analysed by intention-to-treat. A per-protocol analysis will be also performed. To evaluate the difference in the score of preoperative anxiety between intervention and control group, Wilcoxon-Mann–Whitney non-parametric test (or *t*-test, as necessary) will be applied. The same test will be calculated to evaluate the difference in the anxiety score between intervention and control group at T0 and T3.

Wilcoxon-Mann–Whitney will be also used to establish if a difference in the children distress will be between intervention and control group. Chi-square test or exact Fisher test will be applied to evaluate difference in the family preparation for hospitalisation and surgery at T1 between group A and B.

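### The main analysis is labelled intention to treat but keeps only caregivers with an observed primary outcome, and the scope of the promised multiple imputation is not stated, so two primary analyses fit the text

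*Protocol article*

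**What the plan says.** Protocol article, Statistical methods for primary and secondary outcomes {20a}: "Data will be analysed by intention-to-treat. A per-protocol analysis will be also performed". For the primary outcome the section names a two-group test without covariates: "To evaluate the difference in the score of preoperative anxiety between intervention and control group, Wilcoxon-Mann–Whitney non-parametric test", with a t-test allowed as the alternative.

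Methods in analysis to handle protocol non-adherence and missing data {20c} repeats the intention-to-treat label and then defines who is analysed: "All randomised subjects with an available main outcome will be analysed in the group to which they were randomised". It ends with "A multiple imputation technique will be used for missing data". No outcome, time point or analysis is attached to that sentence.

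Outcomes {12} places the primary measurement "before the caregiver and child go into the operating theatre on the day of surgery, approximately seven days after enrolment" (T2 in the participant timeline). Methods for additional analyses {20b} plans no further analyses. Apart from the per-protocol analysis, no secondary or sensitivity analysis is therefore named in which imputation could sit.

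**The concern.** The two sentences in {20c} pull in different directions for the primary outcome. If the main set requires an observed T2 score, nothing is left to impute in it, and the label promises more than the set delivers. If T2 is meant to be imputed, every randomised caregiver is analysed and the restriction to observed outcomes is wrong.

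Two competent analysts could therefore report different primary results, each faithful to the text. The trial is open-label with unblinded assessors (Who will be blinded {17a}) and the outcome is self-reported, so the choice could be made once results by arm are visible. On the available-case reading, the protection that randomisation gives is also weakened if caregivers who lack T2 differ from those who have it.

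**Working it through.** **1. The rules side by side**

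| Reading | Who is in the primary analysis | What imputation does for the primary result |
|---|---|---|
| Set definition in {20c} governs | Randomised caregivers with an observed T2 score | Nothing: no T2 score in the set is missing, and the test has no covariates to fill |
| Imputation covers T2 | All randomised caregivers | Supplies the missing T2 scores |

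No other section chooses between the rows. {20a} repeats the label, and {20b} adds no analysis.

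**2. The plan's own sample size**

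Inputs from Sample size {14}: control mean "of 50 for the control group, with a standard deviation (SD) of 13"; intervention mean 45, SD 10; alpha 0.05; beta 0.20; Wilcoxon-Mann–Whitney test.

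- Pooled SD = √((13² + 10²)/2) = √134.5 = 11.60
- Effect size = 5/11.60 = 0.431, matching the stated 0.43
- Noncentral t with n multiplied by 3/π (Wilcoxon efficiency under normality), two-sided: 90 per arm, power 80.2%

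The stated 180 is reproduced. Sidedness is not stated, but two-sided gives 90 per arm and one-sided would give 71. All 90 per arm must have an observed T2 score, because there is no allowance for loss.

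**3. Power of the available-case Wilcoxon test (loss rates assumed; the article gives none)**

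| Loss in each arm | Observed per arm | Power |
|---|---|---|
| 0% | 90 | 80.2% |
| 5% | 86 (85.5 rounded) | 78.4% |
| 10% | 81 | 75.9% |
| 15% | 76 (76.5 rounded) | 73.2% |
| 20% | 72 | 70.9% |

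This shows what lost T2 scores cost. Imputation would recover only as much as the other collected variables predict of T2.

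**4. Bias of the available-case difference in means**

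Within an arm, let p be the fraction missing and g the observed mean minus the mean of those missing. The full-arm mean is (1 − p) × observed + p × missing, so the observed mean is off by p × g. For the comparison of arms A and B:

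bias = p_A × g_A − p_B × g_B

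Assumed inputs, loss in one arm only:

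| Missing in that arm | Gap 5 points | Gap 10 points | 10-point case as share of planned 5 |
|---|---|---|---|
| 5% | 0.25 | 0.5 | 10% |
| 10% | 0.5 | 1.0 | 20% |
| 15% | 0.75 | 1.5 | 30% |

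A 10-point gap is large: 10/11.60 = 0.86 SD. Two boundary cases matter:

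- 10% missing in both arms with the same 10-point gap: 0.10 × 10 − 0.10 × 10 = 0.
- Unequal loss between arms that is random within each arm: g_A = g_B = 0, so bias = 0.

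**The case against.** The best defence is that both sentences can be obeyed. The set definition is specific to the main analysis and the imputation sentence is general. Imputation has plausible targets elsewhere:

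- follow-up (T3) questionnaires, collected by emailed link because some families do not return;
- health-literacy answers, where the don't-know option is coded as missing;
- single unanswered anxiety items.

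The details of an imputation model may also be left to a fuller document. This defence stands in part. A reader might infer that the paragraph is flatly unworkable, and the text does not support that. But the article never limits imputation in this way. Even if it did, the main analysis would remain an available-case analysis under an intention-to-treat label. The defect is the rule for the primary set, not missing modelling detail.

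A reader might also infer that imputation cannot be combined with the planned test, because Rubin's rules pool an estimate and its standard error. That goes too far. {20a} also allows a t-test, whose mean difference pools directly, and the Mann-Whitney probability has an estimate and a variance as well.

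Finally, T2 is completed on a hospital tablet before surgery with the caregiver present, and app timing is adjusted if surgery is postponed. Loss at T2 is therefore likely to be small, and the outcome more exposed to loss is T3, which is secondary. This stands and lowers the severity.

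**Conclusion.** The point holds at moderate severity. As written, {20c} fixes an available-case main set, calls it intention to treat, and promises imputation that cannot act on the primary outcome within that set. Two primary analyses are compatible with the text and nothing in the article selects one.

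It would be wrong to read this as showing that the primary result will be biased. Bias requires that, within an arm, caregivers missing T2 differ from those observed and that this does not cancel between arms; loss that depends on arm alone does not bias the difference in means. The size is unknown. The 0.5 to 1.5 points rest on assumed loss of 5% to 15% in one arm only and an assumed 10-point gap, neither of which has a source in the article. The sample size of 180 is correct on its own inputs and is not affected.

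**What to change.** State one rule in {20c} before any analysis by arm.

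**Preferred.** Analyse all randomised caregivers as allocated. Impute missing T2 state anxiety separately by arm from T0 state anxiety, T0 trait anxiety and the other baseline variables. The article already collects these: "Caregivers are asked to complete both forms at T0 to determine anxiety trait and baseline levels". Estimate the mean difference by t-test or linear model in each imputed set, ideally adjusted for T0 state anxiety, and pool by Rubin's rules. Report the available-case and Wilcoxon analyses as sensitivity analyses. The participant timeline {13} places T0 after allocation, so first confirm that T0 anxiety was completed before the caregiver knew the arm; if it was not, do not adjust for it.

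**Alternative.** Keep the present set, name it available-case, and state that imputation applies only to listed other outcomes or items.

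**Cost.** A few sentences, a little programming and no new data. The preferred option moves the primary result from the Wilcoxon test to a mean difference. By the calculation above without the 3/π factor, the unadjusted t-test needs 86 per arm, and 90 per arm gives 82.0% power, so the sample size still serves.

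**Limit.** This imputation assumes missing at random given the variables used. It does not remove bias if loss depends on the unobserved T2 anxiety itself.

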### Plans to give access to the full protocol, participant-level data, and statistical code {31c}

The study protocol and data analysis will be available from the corresponding author on request.

## Oversight and monitoring

### Composition of the coordinating centre and trial steering committee {5d}

The IRCCS Burlo Garofolo is the coordinating centre and is responsible for providing day-to-day support to the surgical department staff and administrative nurses in organising the data collection and management of the study. The trial steering committee is composed of the study investigators and an epidemiologist from IRCCS Burlo Garofolo and a researcher from the Area Science Park. The members of the committee agreed on the final protocol and ensure that the study is conducted rigorously. They are responsible for all aspects of study management, from supervising participant enrolment to reviewing data quality. They have also trained the paediatric surgery nurses and administrative nurses in data collection. They monitor the overall conduct of the clinical trial and meet once a month to oversee the conduct and progress of the study.

### Composition of the data monitoring committee, its role and reporting structure {21a}

Considering the low risks of the study, no external data monitoring committee was appointed.

The trial steering committee monitor the conduct of the study and ensures that all phases of the trial are conducted with rigour.

### Adverse event reporting and harms {22}

The study aims to evaluate a low-risk intervention, and no serious adverse events are expected because the intervention consists of providing selected information through a device. Potential risks due incorrect use of the app were not considered relevant to mention.

### Frequency and plans for auditing trial conduct {23}

Considering the low-risk and brief intervention, no audits are planned for this study.

### Plans for communicating important protocol amendments to relevant parties (e.g. trial participants, ethical committees) {25}

If important protocol amendments are required, a request for approval of the changes will be forwarded to the regional ethics committee for approval. After approval, the new version of the protocol will be sent to ClinicalTrials.org. Finally, the entire research team will be informed of the changes at a meeting in a surgical department meeting room and through written information sent via institutional e-mail. Trial participants will be informed from the surgical ward nurses and study informed consent forms.

### Dissemination plans {31a}

The results of the study will be disseminated to the scientific community through scientific publications and presentations at conferences. In addition, the results of the study will be shared with citizens through the hospital’s website and through the media and social media.

## Discussion

Tonsillectomies and adenotonsillectomies are characterised by a short hospital stay and little time for healthcare providers to inform and educate families in a family-centred manner. To our knowledge, no mobile health application has been tested in Italy to support children, their caregivers, and, consequently, their healthcare professionals in the ORL perioperative period. Therefore, if the developed app proves successful, it could be useful for other Italian children undergoing these procedures and their families. Furthermore, it can be later translated into other languages to be available and helpful for other countries or foreigners in Italy. Such a solution can introduce a new and safe management model in paediatric healthcare. It provides families with access to an easily consumable format with evidence-based health content as part of the ORL operation process, leading to continuity of care and empowerment of citizens in terms of positive health management and access to health services.

In general, the app to be implemented aims to strengthen the offer of services to support collaboration between professionals and the interaction between professionals and citizens; to promote the empowerment of citizens in relation to health services; to propose and validate a new management model the health and social care.

The presented solution can enable a family-centred and easily consumable format of the presented evidence-based content and introduce a new management model in paediatric healthcare and education.

## Trial status

Study protocol RC 03/2022. Recruitment started on 16 December 2022. Time for enrolment since starting: 1 year*.* The estimated end date of the study is December 31, 2023.

## Data Availability

All data will be accessed by researchers of IRCSS Burlo Garofolo, University of Trieste and Area Science Park. Relevant data will be made accessible through publication to the scientific community and the public.

## Abbreviations

CE: Conformité Européene [in English: European Conformity]
D.L.: Decreto Legislativo [in English: Legislative Decree]
HLS-EU-Q16: European Health Literacy Survey Questionnaire
IEC: International Electrotechnical Commission
IRCCS: Istituti di Ricovero e Cura a Carattere Scientifico [in English: Scientific Hospitals and Care Institutes]
GDPR: General Data Protection Regulation
mHealth app: Mobile health application
NIS: Network and information systems
ORL: Otorhinolaryngology
SAS: Statistical analysis system
SD: Standard deviation
SPIRIT: Standard Protocol Items: Recommendations for Interventional Trials
mYPAS: Yale Preoperative Anxiety Scale
